**Fig. 1 Fig1:**
[figure not shown]
Diagram of the study protocol according to CONSORT

The NIV group will receive NIV as the initial mechanical ventilation (MV) strategy, irrespective of whether IMV is used later during the following treatment. The IMV group will receive IMV as the initial MV strategy, irrespective of whether NIV is used later during the following treatment (Fig. 2).

**Fig. 2 Fig2:**
[figure not shown]
Study design of the VENIM trial. ARF, acute respiratory failure; FiO_2_, fractional inspired oxygen; IMV, invasive mechanical ventilation; IPAP, inhale positive airway pressure; NIV, non-invasive ventilation; PEEP, positive end-expiratory pressure; VT, tidal volume. BiPAP, bi-level positive airway pressure

#### Implementation of interventions

##### NIV

NIV will be delivered to the patient through a mask with built-in oxygen transport tube. The mask will be adjusted and connected to a ventilation system with oxygen concentration monitor. The initial mode will be BiPAP. In all patients, the settings of NIV will be titrated by a standard protocol: the initial settings for positive end-expiratory pressure (PEEP), FiO_2_ and Inhale Positive Airway Pressure (IPAP) will be 2 cm H_2_O, 40% and 10 cm H_2_O, respectively. PEEP levels will be adjusted in increments of 2 to 3 cm H_2_O, up to a level of 10 cm H_2_O, to obtain a FiO_2_ < 70%. All settings will be adjusted every 10 min to achieve oxygen saturation ≥ 90%, a respiratory rate < 25 breaths/min, disappearance of accessory muscle activity, and arterial blood gas tests showing PaO_2_ 60–90 mmHg, PaCO_2_ 35–45 mmHg, pH 7.35–7.45. Periods of NIV will last at least 1 h and alternate every 4 h with periods of spontaneous breathing, mouth cleaning or feeding. During 30 to 40 min’ intervals, patients breathe oxygen spontaneously while pulse oxygen saturation is continuously monitored and can be maintained above 90%.

We will continuously monitor arterial oxygen saturation, heart rate and respiratory rate in all patients. Once stabilized, patients will be reassessed every 1 h to decide the duration of NIV treatment, according to clinical assessment by the primary care team without any involvement in the research team based on the following criteria.

Criteria for NIV weaning: NIV support will be reduced progressively in accordance with clinical improvement and eventually discontinued when the patient maintains a respiratory rate < 25/min and PaO_2_ > 85 mmHg with FIO_2_ < 50% and PEEP <5 cm H_2_O and relief of respiratory distress for a period of at least 12 h.

Criteria for intubation: Patients in whom NIV fails will undergo endotracheal intubation and receive IMV. The predetermined criteria for intubation are: persistent or worsening respiratory failure at any time during the NIV treatment (high parameter settings of NIV such as FiO_2_ > 70%, PEEP > 10 cm H_2_O or IPAP > 20 cm H_2_O, failure to maintain a PaO_2_/FiO_2_ ratio > 85, respiratory rate > 35/min, PaCO_2_ > 50 mmHg or a pH < 7.30, hemodynamic instability, face mask intolerance, airway bleeding, neurological deterioration, persistent vomiting and non-compliance with NIV treatment.

##### MV

IMV will be initially performed by using the volume controlled mode, but could be adjusted to pressure controlled mode or other modes based on clinical situation such as diseases easy to develop pneumothorax, etc. The initial settings for positive end-expiratory pressure (PEEP), FiO_2_ and tidal volume (VT) will be 5 cm H_2_O, 40% and 6 ml/Kg. PEEP levels will be adjusted in increments of 2 to 3 cm H_2_O, up to a level of 20 cm H_2_O, to maintain oxygen saturation > 90%. Similar to the NIV group, the duration of IMV periods will be decided by the primary care team based on the following criteria.

Criteria and procedure for IMV weaning: IMV support will be reduced progressively in accordance with clinical improvement and discontinued if the cause for respiratory failure has been controlled, the patient maintains a respiratory rate < 25/min and PaO_2_ > 85 mmHg with FIO_2_ < 50% and PEEP <5 cm H_2_O for a period of 12 h. After a successful result of spontaneous breathing trials (including the endotracheal tubing oxygen supply, the pressure support lower than 5 cm water, or continuous positive airway pressure lower than 5 cm water for 30 min, and the Rapid Shallow Breathing Index (Tobin Index) is less than or equal to 105) has been obtained, the endotracheal tube will be extubed, and IMV support will be transferred to oxygen support via Venturi mask.

##### Concomitant medication

Supportive treatment and other necessary therapy will be given based on each patient’s clinical situation, which might include antimicrobial agents on time, diuretics, immunosuppressive agents, corticosteroids, granulocyte-colony stimulating factor, paraenteral nutrition, and crystalloids to maintain optimal volume status and to correct electrolyte abnormalities.

### Study outcomes

#### Primary endpoint

30-day all-cause mortality is the primary endpoint, which will be collected on the 30th day after patient inclusion. Information of the discharged patients will be collected via a phone call to the patient or his/her family members.

#### Secondary endpoints

In-hospital mortality.Length of stay in hospital.Length of mechanical ventilation.Nosocomial infections (diagnosed according to the criteria of Centers for Diseases Control and Prevention [34]).Seven-day organ failure as indicated by the Sequential Organ Failure Assessment score.Adverse events of intervention (such as facial ulceration, stomach dilatation).Failure of mechanical ventilation: The transfer of NIV to IMV as well as death within 30 days in NIV group will be considered as failure of NIV; Death within 30 days in IMV group will be considered as failure of IMV.)Improvement of oxygenation: increase of oxygenation index by 100 compared to baseline or to 200 and above after 45 min of mechanical ventilation.Continuous improvement of oxygenation: Improvement of oxygenation could be maintained till weaning or transfer of mechanical ventilation. Proportion of patients intubated at 30 days (both groups). Proportion of patients intubated and weaned at 3 days (both groups). Ventilator-free days Proportion and timing of tracheostomy.

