### Sample size

The hypothesis of the present trial is that 30-day all-cause mortality in patients treated with NIV will be lower than those treated with IMV. According to previous studies, the mortality rate of ARF immunocompromised patients is from 30% to 90% [1–4]. We used the data from the Fig. 4 of our previous meta-analysis to calculate the sample size, i.e. 30-day mortality in IMV-treated patients of 125/168 (75%) [21], and 85/168 (50%) [21] in NIV-treated patients, 88 patients are needed in each group to establish non-inferiority with 90% power and a 1-sided 5% type I error rate. Assuming that 25% of patients would be lost after the enrollment, thus at least of 236 patients are required.

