### Statistical analysis

All data will be analyzed based on the intention-to-treat (ITT) principle. All analysis results and findings will be reported according to CONSORT statement recommendations [37]. Descriptive statistics will be used to comparing the baseline features of the groups established by randomization. All tests will use a significance level of 0.05 and be performed using SAS 9.4 (TS level 1 M2; Cary, NC, USA).

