#### Secondary endpoints

Continuous variables including length of stay in hospital, length of mechanical ventilation and seven-day organ failure will be reported as mean and standard deviation or as median and interquartile range, and compared between the two groups using Wilcoxon tests. Dichotomous variables including in-hospital mortality, nosocomial infections, adverse events of intervention, failure of mechanical ventilation and improvement of oxygenation will be reported as absolute and relative frequencies, and compared with the χ^2^ test between the two groups. Similar subgroup analysis procedures described above for primary endpoint will also be used. Kaplan-Meier estimator will be used to compare median hospital and ICU length of stay between the two groups. The event of interest and the censoring event are discharge alive and death, respectively. Intubation rate in NIV group and weaning rate in IMV group will be reported as absolute and relative frequencies. Independent variables associated with intubation rate and weaning rate will be explored with Logistic analysis model with a *p* < 0.03 in a step-by-step, backward-forward approach. In accordance with our hypothesis, the ventilatory approach and disease severity will be both forced in the model.

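### Failure of mechanical ventilation counts intubation or death in the NIV arm but only death in the IMV arm, so the planned chi-square comparison of this secondary endpoint is biased against NIV

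*Protocol article*

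**What the plan says.** Protocol article, Study outcomes, Secondary endpoints, gives one endpoint two definitions:

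- NIV arm: "The transfer of NIV to IMV as well as death within 30 days in NIV group will be considered as failure of NIV".
- IMV arm: "Death within 30 days in IMV group will be considered as failure of IMV".

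Protocol article, Statistical analysis, Secondary endpoints, places that endpoint among the dichotomous outcomes tested between the groups: "failure of mechanical ventilation and improvement of oxygenation will be reported as absolute and relative frequencies, and compared with the χ^2^ test". The opening of the statistical analysis section sets the level: "All tests will use a significance level of 0.05". The subgroup procedures planned for the primary endpoint are extended to the secondary endpoints, so they apply to this one too.

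Two other places show that intubation after NIV is an expected part of the NIV strategy. Study interventions states: "The NIV group will receive NIV as the initial mechanical ventilation (MV) strategy, irrespective of whether IMV is used later". The NIV implementation section states: "Patients in whom NIV fails will undergo endotracheal intubation and receive IMV", and lists predetermined criteria for doing so.

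**The concern.** The NIV definition is the IMV definition plus one more way to fail. That extra component has no counterpart in the IMV arm. Those patients are intubated by assignment, and neither reintubation nor failed weaning is counted. A test of equal proportions is meaningful only if the same event is counted on both sides.

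At stake is the reading of a secondary endpoint whose name sounds like a verdict on the ventilation strategy. If mortality is equal, the test is pushed towards finding NIV worse. If NIV lowers mortality, intubation of survivors can hide part or all of that benefit, or reverse it. The trial could meet its primary endpoint while this endpoint shows nothing or points the other way, because of how it was defined.

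**Working it through.** **Inputs from the protocol**

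- Failure definitions and the chi-square test: as quoted above; two-sided level 0.05.
- Design mortality at 30 days: 75% IMV and 50% NIV (Sample size; Interim analysis).
- Size: 88 per arm before loss, 236 in total after 25% loss (same sections).

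**Input not in the protocol**

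- q, the share of NIV-arm 30-day survivors who were intubated. Assumed range 10% to 50%, with 60% as one further case.

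**Step 1. The plan's own sample size.** The protocol gives no figure for the failure endpoint, so its sample size serves only to scale the illustration. For 75% v 50%, 90% power and a two-sided test with continuity correction, the pooled two-proportion formula gives 85 per arm at 0.05. At the final O'Brien-Fleming nominal level of 0.046259 it gives 87, within two of the stated 88. Loss: 88 / (1 − 0.25) = 117.3, rounded up to 118 per arm, and 2 × 118 = 236, as stated. Both 88 and 118 per arm are used below. Because the analysis is by intention to treat, 118 is the upper bound.

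**Step 2. Size of the shift.** With mortality m_N (NIV) and m_I (IMV):

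- NIV failure = m_N + (1 − m_N) × q
- IMV failure = m_I
- Difference in failure = (m_N − m_I) + (1 − m_N) × q

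The second term is never negative, and it is positive as soon as one NIV survivor has been intubated. The direction of the bias needs no assumption; its size depends on q.

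**Step 3. Equal mortality.** The chance of p<0.05 against NIV is Φ[(d − 1.96 × se0) / se1]. Here d is the difference in failure, se0 the pooled and se1 the unpooled standard error, without continuity correction.

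Worked case: m = 0.50, q = 0.30, 88 per arm.

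- NIV failure 0.50 + 0.50 × 0.30 = 0.65; d = 0.15; pooled proportion 0.575.
- se0 = √(0.575 × 0.425 × 2/88) = 0.0745.
- se1 = √((0.65 × 0.35 + 0.50 × 0.50)/88) = 0.0737.
- Φ[(0.15 − 1.96 × 0.0745)/0.0737] = 0.52.

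| Mortality, both arms | q | NIV v IMV failure | Excess (points) | 88 per arm | 118 per arm |
|---|---|---|---|---|---|
| 50% | 10% | 55.0% v 50% | 5.0 | 0.10 | 0.12 |
| 50% | 30% | 65.0% v 50% | 15.0 | 0.52 | 0.65 |
| 50% | 50% | 75.0% v 50% | 25.0 | 0.94 | 0.98 |
| 62.5% | 10% | 66.3% v 62.5% | 3.8 | 0.08 | 0.09 |
| 62.5% | 30% | 73.8% v 62.5% | 11.3 | 0.36 | 0.46 |
| 62.5% | 50% | 81.3% v 62.5% | 18.8 | 0.80 | 0.90 |
| 75% | 10% | 77.5% v 75% | 2.5 | 0.06 | 0.07 |
| 75% | 30% | 82.5% v 75% | 7.5 | 0.23 | 0.29 |
| 75% | 50% | 87.5% v 75% | 12.5 | 0.57 | 0.69 |

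For comparison, an outcome defined the same way in both arms would reject against NIV in about 2.5% of trials when there is no difference (5% over both directions).

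**Step 4. The protocol's design mortality (NIV 50%, IMV 75%).** NIV failure = 50% + 50% × q; IMV failure = 75%.

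| q | NIV failure | NIV minus IMV (points) |
|---|---|---|
| 0% | 50% | −25 |
| 10% | 55% | −20 |
| 30% | 65% | −10 |
| 50% | 75% | 0 |
| 60% | 80% | +5 |

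At q = 30% the chance that the test shows an NIV advantage is 0.30 with 88 per arm and 0.39 with 118. If failure meant death in both arms, it would be 0.94 and 0.98.

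**The case against.** **It is one secondary endpoint among many, and the parts are visible.** This stands, and it sets the severity. The primary endpoint, 30-day mortality, is defined alike in both arms. The sample size and early stopping for a difference between arms rest on mortality. Mortality is reported by arm, the NIV intubation rate is reported separately, and the proportion intubated at 30 days is a listed endpoint for both groups. A careful reader could see where an excess in failure came from. That limits the damage but does not make the test valid.

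**The wording could mean that both events must occur.** On that reading an NIV patient who was intubated and survived would not count as a failure, which does not fit the NIV section, where failing NIV leads to intubation. Nor would it cure the asymmetry: NIV failures would then be only a subset of NIV deaths, against all deaths in the IMV arm.

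**The comparison might be meant as description.** The statistical analysis section treats the two cases differently. The NIV intubation rate is to be given as frequencies only, whereas failure is listed for a between-group test.

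**The size depends on an unstated q.** True. At q = 10% the chance of a significant result against NIV is only 6–12% across the two arm sizes, and at the design mortality the benefit vanishes only if half of NIV survivors are intubated.

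**Stronger readings that a reader might infer.** One is that the test will declare NIV worse whenever mortality is equal. The table in the working does not support this: at low q, significance is unlikely. Another is that the p-value reflects the definition alone. Death is in both definitions, so a large enough mortality benefit would still show through.

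**Conclusion.** The point holds as a should-fix for one secondary endpoint. The two definitions differ by one component that only the NIV arm can meet, the protocol tests them against each other, and nothing elsewhere in the article supplies a common definition or withdraws the test.

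The bias against NIV is (1 − m) × q. Its direction is certain once any NIV survivor is intubated. With equal mortality of 50–75%, the chance of p<0.05 against NIV is:

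- q = 10%: 7–12% with 118 per arm, 6–10% with 88.
- q = 30%: 29–65% with 118 per arm, 23–52% with 88.
- q = 50%: 69–98% with 118 per arm, 57–94% with 88.

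These figures rest on the assumed q, on reading the NIV definition as either event, and on a normal approximation without continuity correction. The finding does not reach the 30-day mortality analysis or the trial's main conclusion, and the documents do not support extending it there.

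**What to change.** In the protocol's Statistical analysis, Secondary endpoints:

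1. Remove failure of mechanical ventilation from the outcomes compared between arms, including the subgroup analyses.
2. Report NIV failure (intubation or death by day 30) within the NIV arm only, with a 95% confidence interval. This fits the interim analysis section, where the data and safety monitoring committee already follows failure of NIV as a single-arm quantity.
3. Limit between-arm tests to outcomes defined identically in both arms, such as 30-day mortality.

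Ventilator-free days, already on the list, are not a ready substitute. The article gives no time horizon, does not say how death is scored, and does not say whether time on NIV counts as ventilation. If only invasive ventilation counted, the asymmetry would return in NIV's favour. The endpoint could serve once the horizon and the scoring of death are fixed and both NIV and IMV time count as ventilation, in the same way for both arms.

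Cost: a wording change to the protocol and one secondary p-value, with its subgroup versions, dropped. No new data are needed.

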### Study population

Patients will be recruited in hospitals where the staffs have considerable experience and expertise in the treatment of immunocompromised patients and application of mechanical ventilation. The inclusion and exclusion criteria are as followings (Table 1):

**Table 1 Tab1:** Inclusion and exclusion criteria

Population characteristics	Inclusion criteria	Exclusion criteria
Demographic characteristics	Adult (18 years old ≤ age ≤ 80 years old) immunocompromised patients with moderate to severe ARF diagnosed within the last 72 h.	Age < 18 or >80 years old.
Diagnosis of mid to severe ARF	85 ≤ PaO_2_/FiO_2_ ≤ 170 adjusted with altitude change or clinically diagnosed with evidence of respiratory distress (intercostal recession or other assisted breathing muscle movements, polypnea >35/min or dyspnea at rest).	(1) Partial pressure of arterial carbon dioxide (PaCO_2_) > 50 mmHg or arterial pH < 7.20; (2) PaO_2_/FiO_2_ > 170(mild) or PaO_2_/FiO_2_ < 85(severe);
Diagnosis of immunocompromised status	At least one of the following: (1) Hematologic malignancy or solid tumor under chemotherapy; (2) Solid organ or stem cell transplant; (3) Long-term (>30 days) and high dose steroids (>1 mg/kg/d prednisone equivalent) usage and/or any other immunosuppressive drugs; (4) Neutropenia (defined as a neutrocyte count of <1.0 × 109/L) showing for at least 48 h.	Other causes of immunocompromise including HIV infection, etc.
Indications for intervention	Patients with severe ARF described above, in which mechanical ventilation is indicated.	Patients have been treated with NIV, IMV or high-flow oxygen therapy within 30 days. NIV is contraindicated or intubation is inevitable, which including PaO_2_/FiO_2_ < 85, respiratory arrest, hemodynamic instability, inability to fit the face mask, pneumothorax, vomiting, development of airway bleeding, inability to protect the airway, or copious respiratory secretions.
Morbidities	Mild diseases not stated in the exclusion criteria.	Acute cardiac failure; Acute-on-chronic ARF; Other severe diseases including dilated cardiomyopathy, valvular heart disease, cardiogenic pulmonary edema, implanted cardiac pacemaker, or acute coronary syndrome; systolic arterial pressure < 90 mmHg after optimal fluid therapy; history of chronic obstructive pulmonary disease (COPD) or asthma; impaired consciousness (Glasgow Coma Scale score < 8) [32]; postoperative acute respiratory failure; pregnancy or breastfeeding.

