#### Exclusion criteria

Patients will be excluded from the study when:Age < 18 or >80 years old;Partial pressure of arterial carbon dioxide (PaCO_2_) > 50 mmHg [32] or arterial pH < 7.20;PaO_2_/FiO_2_ > 170 mmHg or PaO_2_/FiO_2_ < 85 mmHg;Patients have been treated with NIV, IMV or high-flow oxygen therapy within 30 days.NIV is contraindicated or IMV is definitely indicated, including PaO_2_/FiO_2_ < 85 mmHg, respiratory arrest, hemodynamic instability, inability to fit the face mask, pneumothorax, vomiting, development of airway bleeding, inability to protect the airway, or copious respiratory secretions;Comorbidity with acute-on-chronic ARF;Comorbidity with acute cardiac failure;HIV positive patients;Comorbidity with other severe diseases, including dilated cardiomyopathy, valvular heart disease, cardiogenic pulmonary edema, implanted cardiac pacemaker, or acute coronary syndrome; systolic arterial pressure < 90 mmHg after optimal fluid therapy; history of chronic obstructive pulmonary disease (COPD) or asthma; impaired consciousness (Glasgow Coma Scale score < 8), [33]; postoperative acute respiratory failure; pregnancy or breastfeeding; Lack of consent, do-not-intubate decision, and any other situations where obvious bias are expected.

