#### Data collection and follow-up

Baseline characteristics will be recorded immediately after inclusion, including age, gender, primary diagnosis, PaO_2_/FiO_2_, causes of ARF and immunocompromised status, preexisting comorbidities, SAPS II, oxygen therapy and other treatment used before the inclusion. The information required for evaluation during study participation will be recorded daily until primary endpoint occurs or until day 30 after inclusion, whichever occurs first. Evaluations include settings of intervention, other treatment, laboratory data, evaluation of ARF, adverse events of intervention and complications developed during hospital stay. Each patient is followed until day 60 or until other endpoints occur, whichever occurs first. The following data are recorded: 30-day survival, length of hospital stay, hospital survival and adverse events of intervention.

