#### Primary endpoint

30-day mortality will be reported as frequency with the 95% confidence intervals and compared between the two groups using the χ^2^ test. We will explore the interaction between treatment effect and baseline disease severity indicated by SAPS II (cut-off value 60) and PaO_2_/FiO_2_ (cut-off value 100). If such an interaction is found, we will further conduct subgroup analysis to explore a treatment effect within each subgroup. Multiple comparisons will be conducted with the Bonferroni test (error of first order 0.025). Similar analysis will be conducted between treatment effect and different causes of immunodeficiency (divided into two subgroups: a. solid tumors or hematologic malignancies, b. immunosuppressive treatment or organ transplant.).

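### Improvement of oxygenation at 45 min is tested only as a yes/no whose required rise runs from 100 down to 30 mmHg with baseline; a baseline-adjusted continuous analysis should be added

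*Protocol article*

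**What the plan says.** Under Study outcomes, Secondary endpoints, improvement of oxygenation is a yes/no: "increase of oxygenation index by 100 compared to baseline or to 200 and above after 45 min of mechanical ventilation". A second endpoint, continuous improvement of oxygenation, is built on the same status.

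Table 1 admits patients with "85 ≤ PaO_2_/FiO_2_ ≤ 170 adjusted with altitude change", and the Exclusion criteria remove "PaO_2_/FiO_2_ > 170 mmHg or PaO_2_/FiO_2_ < 85 mmHg". The alternative entry route by clinical signs of respiratory distress therefore does not widen the baseline range.

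Data collection and follow-up states: "Baseline characteristics will be recorded immediately after inclusion, including age, gender, primary diagnosis, PaO_2_/FiO_2".

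Statistical analysis, Secondary endpoints, names the test: "improvement of oxygenation will be reported as absolute and relative frequencies, and compared with the χ^2^ test between the two groups". No covariate enters this comparison. Baseline PaO2/FiO2 appears only in the interaction and subgroup work described for the primary endpoint, "baseline disease severity indicated by SAPS II (cut-off value 60) and PaO_2_/FiO_2_ (cut-off value 100"), which is carried over to the secondary endpoints.

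**The concern.** The rule joins two hurdles, a rise of 100 or reaching 200, and which one is easier depends on where the patient starts. Two patients with the same gain can be scored differently only because their baselines differ.

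Three things are at stake:

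- **Efficiency.** A measured ratio is reduced to a yes/no, and a recorded baseline that predicts it is left out of the main comparison.
- **Interpretation.** The responder percentage reflects starting severity as well as response.
- **Subgroups.** The planned cut at 100 is the point where the rule changes, so the two severity strata face different hurdles.

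Mortality, the primary endpoint, is not touched.

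**Working it through.** **The plan's own size figure.** The article sizes the trial on mortality only and gives no power for oxygenation. For 0.75 v 0.50, 90% power, continuity correction and the stated final nominal alpha of 0.046259, the usual formula gives 87 per group, against the stated 88. Allowing for 25% dropout, 88/0.75 = 117.3, so 118 per group and 236 in total, as stated. I use 88 per group below.

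**Required rise (document figures only).** A responder needs a 45-min value of at least min(baseline + 100, 200), so the required rise is min(100, 200 − baseline). The two routes meet at a baseline of 100.

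**Dependence on baseline (assumed inputs).** Give every patient the same rise distribution, mean 50 and SD 60 mmHg. The chance of response is then 1 − Φ((required rise − 50)/60).

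| Baseline | Required rise | Chance of response |
|---|---|---|
| 85–100 | 100 | 1 − Φ(0.833) = 20% |
| 120 | 80 | 1 − Φ(0.500) = 31% |
| 140 | 60 | 1 − Φ(0.167) = 43% |
| 170 | 30 | 1 − Φ(−0.333) = 63% |

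**Effect on the subgroup comparison.** Add a constant benefit of 29.3 mmHg, so the treated mean rise is 79.3.

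- At a baseline of 85–100, response goes from 20.2% to 1 − Φ(0.345) = 36.5%, a ratio of 1.81.
- At 170 it goes from 63.1% to 1 − Φ(−0.822) = 79.4%, a ratio of 1.26.

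The difference is about 16 points in both, so one uniform effect looks alike or unlike across strata depending on the scale.

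**Power.** Assumptions, none of them in the article: baseline uniform on 85–170, mean control rise 50, and a constant shift between arms set so that ANCOVA has about 90% power, δ = SD × (1.960 + 1.282) × √(2/88). For a residual SD of 60 this is 29.3 mmHg. Two-sided 0.05, 88 per group, 600 simulated trials per row (standard error about 2 points).

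| Residual SD | Baseline slope | Chi-square on responder | Logistic, responder + baseline | ANCOVA |
|---|---|---|---|---|
| 40 | 0.5 | 74% | 73% | 92% |
| 40 | 1.0 | 58% | 65% | 90% |
| 60 | 0.5 | 74% | 72% | 90% |
| 60 | 1.0 | 68% | 72% | 90% |
| 80 | 0.5 | 75% | 73% | 90% |
| 80 | 1.0 | 69% | 70% | 89% |

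With a smaller control rise the chi-square falls further. At mean rise 20, SD 40, slope 1 and a truncated-normal baseline it has 51% against 90%. Over the range of settings it has roughly 50–75%.

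**Source of the loss.** In the central case (SD 60, slope 1) power is 68% for the chi-square, 86% for an unadjusted t-test on the 45-min value and 90% for ANCOVA. Adding baseline to the yes/no recovers little. Most of the loss is from dichotomising; omitting baseline adds about 0–12 points on the continuous value.

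**Limit on the correlation.** A uniform baseline on 85–170 has SD 85/√12 = 24.5. A correlation of 0.7 with a 45-min SD of 50 or 70 would need a slope of 0.7 × 50/24.5 = 1.43 or 0.7 × 70/24.5 = 2.0. That is implausible, so gains calculated at such correlations are not used.

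**A different effect shape.** Suppose 30% v 50% of patients have an extra jump averaging 90 mmHg and the others none. Chi-square v ANCOVA is then about 45% v 53% (jump SD 40) or 39% v 38% (jump SD 80).

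**Validity.** With no true difference, the chi-square rejected in about 5% of simulated trials.

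**The case against.** A prespecified responder threshold is a legitimate choice, and a mean difference answers a different question. This is one unpowered secondary endpoint among many, the document contains no contradiction here, and a supportive continuous analysis may sit in a statistical analysis plan that is not shown. All of this stands and keeps the point minor. It does not remove it, because the article itself fixes both the rule and its test.

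The advantage of ANCOVA also depends on the effect shape: a constant shift favours it, and a benefit confined to some patients can erase the gain. That stands, and the size is stated with that condition.

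A reader might infer more than the document supports:

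- **That the comparison is biased or invalid.** Randomisation gives both arms the same expected baseline distribution, and chance imbalance is covered by the test's error rate.
- **That baseline PaO2/FiO2 is ignored.** It is used for interaction and subgroup work at 100, though not as a covariate.
- **That the trial's only physiological comparison is weakened.** Seven-day organ failure by SOFA and continuous improvement of oxygenation are also listed.
- **That the responder endpoint should be demoted.** Continuous improvement of oxygenation is defined from it, so it has to stay.

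**Conclusion.** The point holds as a low-severity improvement. The required rise of 100 down to 30 mmHg, and the switch at the subgroup cut of 100, follow from the article's own figures once oxygenation index is read as PaO2/FiO2. The article does not define the term, but this reading fits the 85–170 entry range and the target of 200.

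The loss is of efficiency and interpretability. Its size rests on assumed inputs: under a constant shift and a baseline slope of at most 1, with 88 per group, roughly 50–75% power for the chi-square against about 90% for ANCOVA; under a benefit confined to a subset, little or no gain. A flat statement that the plan throws away much of its power would go too far, since the article gives neither the spread of the ratio nor the shape of the effect.

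**What to change.** In Statistical analysis, Secondary endpoints:

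1. Add a prespecified linear regression of 45-min PaO2/FiO2 (log scale if skewed) on randomised arm, baseline PaO2/FiO2 and centre, which is the randomisation stratum. Report the adjusted mean difference with its 95% CI.
2. Use this continuous outcome for the PaO2/FiO2 subgroup analysis, so that both strata are judged on the same scale.
3. Keep the responder proportion and its chi-square as a reported secondary result, because continuous improvement of oxygenation depends on it.
4. State that oxygenation index means PaO2/FiO2.

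The cost is analysis wording: both values are already needed to score the responder. The small downside is one more analysis, on a mean-difference scale that is less directly clinical than a percentage of responders.
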